### Step 4: Program Production

In *step 4* of IM, the program is produced and pretested. In the sections below, we describe the specific content of the intervention, the adaptation of the program components, and the pretest.

#### Scope and Sequence

*MyLifestyleCoach* consists of an introductory session (opening session) and the modules *I Eat* and *I Move*. The program is designed in such a way that participants can choose which behavioral change module (or no module) they want to follow and if they are interested in following both modules, which module they want to visit first and when they want to use the other module. See Figure 1 for the structure of the program. Both *I Eat* and *I Move* consist of 4 sessions. Figure 2 presents the content of all the sessions (this figure has been adapted, with permission from Friederichs et al [12]).

**Figure 1 figure1:**
[figure not shown]
Overview of the *MyLifestyleCoach* intervention. FFQ: Food Frequency Questionnaire; SQUASH: Short QUestionnaire to ASsess Health.

**Figure 2 figure2:**
[figure not shown]
Overview of the content of the sessions of *I Eat*. PA: physical activity.

#### Opening Session

Before using the opening session, participants have to complete a questionnaire on several topics, including current dietary behavior and PA level, so that feedback about these behaviors can be provided. In the introduction to the opening session, participants become acquainted with the content of the program and meet the video coaches who will guide them through the program. These video coaches are used to create a sense of relatedness. Furthermore, participants receive general feedback about their current diet and PA level based on the results of the baseline questionnaire they completed beforehand. Feedback is provided using a traffic light system: The color of the light that is displayed indicates how closely their current PA level and diet correspond to health recommendations and which module (*I Eat* and/or *I Move*) is advised to use. The traffic lights are purely meant to provide participants with an insight into what they could change and are not necessarily intended to induce compliance with PA guidelines and dietary recommendations. When participants received a green traffic light advice (in line with the guidelines), they received the message that following the correspondent module was not of high priority. Nevertheless, they were free to have a look at the module. When participants received an orange traffic light advice, they received the message that following the correspondent module might be relevant to them. When participants received a red traffic light advice, they received the message that following the correspondent module might be highly relevant to them. For both the orange and red traffic light advice, they were told that they were free to have a look at the module by choosing it in the program later. Participants also have to use the importance ruler to rate how important they feel it is for them to eat more healthily and become more physically active. They are given feedback tailored to their ratings. Subsequently, participants receive a short, combined summary of their current dietary behavior and PA level, and again are given advice on which module to use. Thereafter, they have to choose whether they want to participate in *I Eat* and/or *I Move*. They are also asked whether they want to start immediately or wait (waiting is restricted to a maximum of 14 days to avoid that the follow-up questionnaires, see Figure 3 [*Start module*], and the sessions of the intervention are intertwined). Figure 3 has been adapted with permission from Friederichs et al [12]. Next, we describe the sessions of the *I Eat* module.

**Figure 3 figure3:**
[figure not shown]
Evaluation design of MyLifestyleCoach. BREQ: Behavioral Regulation in Exercise Questionnaire; FFQ: Food Frequency Questionnaire; PA: physical activity; PCS: perceived competence scale; SQUASH: Short QUestionnaire to ASsess Health; TSRQ: Treatment Self-Regulation Questionnaire.

#### I Eat Session 1

Session 1 is the most extensive of the 4 interactive sessions. It starts with an introduction, which includes the Dutch definition of a healthy diet, and is intended to engage participants. Thereafter, participants’ awareness about their current dietary behavior is raised through the provision of detailed feedback (in terms of daily amount of vegetables, portions of fruit, consumption frequency of snacks, and weekly consumption of fish). The importance participants place on changing their behavior and their confidence in their ability to do so are critical to autonomous motivation. We assess how important they perceive healthier eating to be and how confident they are of achieving this using the importance and confidence ruler (1-10 scale) [43]. Follow-up questions are then asked based on the scores given. For example, “How important would you say it is for you to eat healthier on a scale ranging from 1 to 10?” For example, scores of less than 4 in response to the question “How important would you say it is for you to eat more healthily on a scale ranging from 1 to 10?” prompt the following: “It looks as if healthy eating is not your top priority, but perhaps there are still reasons why eating more healthily is important to you. Why could eating more healthily be important to you?” (see Multimedia Appendix 3 for more detailed information regarding these applications). Finally, intention to change (which is related to intrinsic motivation) is addressed. Users who say they intend to change are asked whether they want to make an action plan for eating more healthily. Participants are asked to formulate their goal in a concrete and realistic manner, formulate their most important motivation for eating (more) healthily, the location(s) of their choice, and on which moments they want to execute their activity. If desired, the participants can also indicate with whom they want to execute this action plan (*relatedness*) and what preparations they need to undertake before being able to implement their plan. In a pilot study of the *I Move* intervention, 85% to 90% chose to make such a plan for increasing their level of PA [44]. If the participant decides to make an action plan, the program stimulates him or her to execute it. The following sessions evaluate participants’ execution of their action plan. Participants who do not want to make a plan at this stage are given the opportunity to do so in the following sessions. At the end of this session (as well as at the end of sessions 2 and 3), participants who chose to do just the *I Eat* module are asked if they would like to start the *I Move* module as well. Those who express an interest in doing so are then asked whether they want to start immediately or select a start date up to 14 days thereafter. If they choose to start the *I Move* module immediately, they are taken to session 1 of *I Move* once they have completed their current session. If they decide to start later with *I Move,* they receive an email on the day they have selected containing a link to session 1 of the module.

#### I Eat Session 2

Three weeks after session 1, participants receive an email inviting them to session 2. Session 2 looks back at the participant’s perception of the importance of healthy eating. Participants are also asked whether they have identified new reasons to eat more healthily. In addition, participants are asked about what effects they think it would have if they started eating more healthily at this point. After that, participants are asked to think of situations in which they would find it difficult to eat healthily and to think of strategies they might use to cope with these situations. Thereafter, the participants are invited to identify personal strengths to boost their confidence. They are asked to elaborate on how their personal strengths (such as perseverance) are helpful in dealing with such difficult situations. This is a helpful strategy in the change process. Finally, the participants who made an action plan to help them eat more healthily in the previous session are given the option to evaluate how well they have succeeded in following it. They are given the opportunity to alter their plan and formulate additional coping plans. Those who did not make a plan are again given another opportunity to do so.

#### I Eat Session 3

At 6 weeks after session 1 (ie, 3 weeks after session 2), participants receive an email invitation to session 3. This session begins with assessment of participants’ current perception of the importance of healthy eating and their confidence in their ability to do so, which is carried out using the rulers. Subsequently, participants are given feedback about how their perceptions compare with their perceptions at the start of *I Eat* (session 1). After the feedback message concerning confidence, the participants are asked to think back to a difficult situation in which they struggled to eat healthily but managed to overcome their difficulties. This is supposed to boost their self-efficacy and give them more confidence in their ability to eat more healthily. They are then given some tips for eating healthily in situations where it is difficult to do so, which are derived from the pilot study. After this topic, participants receive feedback on whether they have made progress toward a healthier diet (comparison of current and preintervention diet, based on the self-assessments). Finally, participants are once again given the option of evaluating and adapting their plans and formulating coping plans. If they have not yet made a personal healthy eating action plan, they are once again given the opportunity to do so.

#### I Eat Session 4

At 3 months after session 1, participants can enter session 4. This is a session in which several topics from previous sessions are covered. Participants can choose which of several topics they would like to pursue. The available topics are feedback on their dietary behavior, long-term personal motivation and confidence, how to deal with difficult situations, and information on how to maintain their new behavior after the end of the program. Participants can opt to skip one or more topics.

#### I Eat Videos

The program gives participants the option of viewing various prerecorded videos during the sessions that are mainly text based. Previous research has shown that this type of interactive video counseling has promise as a technique for public health interventions [45-48]. These videos include a human video coach who guides the participant through the program, short videos telling the stories of 4 putative *former participants* of *I Eat* (an older nurse, a younger cleaning lady, an older production assistant, and an elementary school teacher), and videos in which a dietician talks about the positive effects of eating healthily. Giving participants the opportunity to select the videos they want to see instead of making them start automatically at a certain point in a session is in line with MI practice and with the principles of SDT, which suggest that the individuals’ need and desire for information should be assessed before it is provided. The videos were scripted, and a film producer was hired to produce them. A real dietician provided feedback on the dietician’s script. An advertisement was placed on a casting website to recruit actors for these videos. To increase the credibility of the actors appearing in the videos, several colleagues in the health psychology department were asked to choose the actors (from a preselection of actors that responded to the advertisement) who were most representative of a certain description. The videos were recorded in different settings, including a green screen, hospital, high school, and domestic setting.

#### Modification of I Move

Effectiveness and reach are key to the impact of a program. *I Move* was innovative because it was one of the first interventions to integrate SDT and MI into a Web-based, CT intervention. Although *I Move* was effective in increasing PA, it was recognized that improvements were necessary to reduce the high dropout rate (607/987 participants, 61.5%, did not complete the 12-month questionnaire) and to broaden the intervention by adding a healthy nutrition module. We fine-tuned the tailoring of the feedback messages and language used to make it more suitable for people with limited education. For example, we changed passive sentences into active sentences. Furthermore, the tailored feedback was updated, so that it was consistent with the new Dutch guidelines for PA (150 min of moderate-intensity PA per week; the original *I Move* intervention focused on the accumulation of 30 min or more of moderate-intensity PA over at least 5 days per week). Finally, we made the guidelines less explicit to encourage users to set their own targets for increasing PA level rather than simply trying to achieve the recommended level.

#### Delivery Channel

As unhealthy dietary patterns are prevalent, it is important to design and implement an intervention that can reach large numbers of people. Computer tailoring can be used to create interventions with some degree of personalization to potentially reach a large population at relatively low costs. Computer-tailoring has been defined as “the adaptation of health education materials to one specific person through a largely computerized process” [49]. It could especially be beneficial in the Netherlands, where the overwhelming majority (97%) of the population aged 12 years and above has access to the internet [50], including low SES groups [51]. There are several reasons to keep computer tailoring as a technique, similar as in *I Move*, to deliver the intervention. First, the CT intervention *I Move* has been shown to be effective in increasing PA [13,14]. Research has also indicated that Web-based, CT dietary interventions are more successful in changing people’s intake of fruit, vegetables, and fat than provision of general guidance or no information [49,52-57]. Finally, CT interventions have also been found to be effective among low SES groups [58].

*MyLifestyleCoach* was developed using the TailorBuilder software (OverNite Software Europe) [59]. This software is designed to generate tailored feedback based on algorithms. The intervention is integrated into a website that provides information about the intervention and answers to frequently asked questions [60].

#### Pretest

We will conduct 2 pretests. The first will be a 3-part paper-and-pencil pretest covering (1) the design of the website, (2) evaluation of the baseline questionnaire, and (3) the opening session (N=10). The first part will use 5-point Likert scales to evaluate several possible website designs in terms of appeal and appreciation. Participants will also be asked to suggest possible improvements. The second part will focus on clarity of the questions and instructions in the baseline questionnaire. The third part will consist of several questions about the content of the opening session, the clarity of explanation of the program structure, the clarity of traffic-light feedback about dietary and PA patterns, and feedback about the importance of eating more healthily and being more physically active. We will also ask which module(s) the participants would choose to follow and why. We will ask about several attributes of the videos, such as how easy it is to relate to the content and narrators and whether they are interesting to watch. The second and third parts of this pretest will be completed once the participant has walked through the opening session on the Web.

In the second pretest, we will test the module *I Eat* (N=16). Overall, 10 participants will test the intervention at home using their own devices. They will receive a printed questionnaire to assess the user experience, which they should fill in as they proceed through the intervention. We will also conduct a qualitative evaluation with 6 other participants and will use the think-aloud method while testing the intervention. The results and suggestions from the pretests will be used to improve and finalize the intervention for the randomized controlled trial (RCT).

### Step 5: Program Adoption and Implementation Plan

The development of an implementation plan to enable adoption, implementation, and maintenance of the program is central to Step 5 of IM. As *I Eat* is also one of the first dietary interventions to integrate MI into a Web-based, CT format, the evaluation study (ie, the assessment of its effectiveness) will focus on the adoption and implementation of *MyLifestyleCoach*.

For adoption of the program in the context of the evaluation study (ie, the intention to use it and subscription to the program), we will provide information about the program through an advertisement that will be distributed via an internet research panel to recruit the participants for this study. Facilitation of program use (for implementation and sustainability) was already taken into account in the first step of the development. Minimal human action is required to participate in the intervention. Individuals who want to participate in the intervention can register to do so on the website. After registering, they will automatically receive invitation emails when a new session is available. Furthermore, several small pilot studies and interviews have been conducted with members of the target population to identify their preferences and needs regarding the content and appearance of the intervention and the intervention has been adapted accordingly. Once we have demonstrated that the program is effective in delivering the intended outcome, that is, eating (more) healthily, we may consider further implementation possibilities, such as targeting other program outcomes in other domains of public health (eg, smoking), and the use of advertisements in mass media, social media, newsletters, or certain websites for sustainability purposes.

#### Participants

The inclusion criteria for the participants are age between 18 and 70 years, an adequate understanding of the Dutch language, possession of a computer or tablet with access to the internet, and no participation in the *I Move* intervention or pilot studies. Participants who are not willing to sign the informed consent will be excluded.

Given the modifications made to the original *I Move* intervention, we expect to improve the ES for PA to 0.30 at 12 months [13,14]). There are no estimates of ES in an MI-planning CT dietary intervention. A review indicates that in clinical settings, MI has produced ESs of up to 0.57 [61], but this is the first Web-based MI-planning CT intervention targeting both PA and dietary habits. It might be possible to find additive effects when participants decide to start with both modules, *I Eat* and *I Move*, so we will use a conservative estimate of the ES (0.30). We expect an ES of 0.05 in the control condition. On the basis of these data, a power calculation (ES=0.25; power=0.80) indicates that a total of at least 400 participants is needed for this study (200 per condition). On the basis of an expected dropout rate of 50%, we would need to enroll at least 800 participants. We do not expect all participants to decide to do both modules, and as we want to analyze the level of participation of the modules, we will enlarge the sample size to at least 1200 participants in total. A research panel will be used to recruit these participants. The sample will be representative of the population in terms of age and gender, but we will strive for an overrepresentation (about 50% instead of the 31% in the population [62]) of people with a low educational level, which will be used as a proxy for SES.

After passing the inclusion questions and providing informed consent, two-thirds of the participants will be randomized into the intervention condition and one-third will be randomized into the waiting list control condition. We will oversample the intervention group, as we expect that many participants will not participate in both modules; oversampling provides the option to conduct separate analyses per module. After that, participants will fill in the baseline questionnaire (dietary and PA parts) and continue with the intervention. The path they follow will depend on the choices they make.

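### The 400-completer, 800-enrolled figure assumes equal arms, but the trial randomises 2:1, so 800 enrolled does not give the stated 80% power

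*Protocol article*

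**What the plan says.** All of this is in the Protocol article, Step 6: Evaluation Plan, under Participants.

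- **Effect.** The intervention arm is assigned an effect size of 0.30. For the comparator, "We expect an ES of 0.05 in the control condition". The difference, 0.25, enters the power calculation.
- **Size.** On these inputs, "a power calculation (ES=0.25; power=0.80) indicates that a total of at least 400 participants is needed for this study (200 per condition".
- **Dropout.** "On the basis of an expected dropout rate of 50%, we would need to enroll at least 800 participants".
- **Enlargement.** Enrolment is then raised to at least 1200. The reasons given are that not everyone will take both modules and that module participation is to be analysed.
- **Allocation.** "two-thirds of the participants will be randomized into the intervention condition and one-third will be randomized into the waiting list control condition". The larger intervention arm is explained as allowing separate analyses per module.

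The subsection gives no alpha, sidedness, analysis model or baseline correlation.

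**The concern.** The calculation is set out for two equal arms and the randomisation is not equal. For a fixed total, a 2:1 split is less efficient than 1:1, so a total that is just enough at 1:1 falls short at 2:1. The article presents 800 as the number that meets the power target and the further 400 as serving module uptake and participation analyses. If 800 does not meet the target for the allocation used, part of that 400 is already needed for the main comparison. A reader would then overestimate the reserve against participants who take one module or none.

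There is a second question about the 200 per arm. It is smaller than the usual two-sided 5% answer for an effect size of 0.25, and the article does not say what produced it.

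**Working it through.** **Inputs from the article:** effect size 0.30 − 0.05 = 0.25 (SD 1, since it is standardised); power 0.80; 200 per condition; dropout 50%; allocation 2:1; enrolment 1200.

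**Assumed, because not stated:** alpha 0.05, with one-sided and two-sided tests both tried; a comparison of two means, without baseline adjustment unless noted; equal dropout in both arms.

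**Formulas.** With k intervention participants per control, control n = (1 + 1/k)(z_α + z_power)² / ES². Power = Φ(ES / √(1/n₁ + 1/n₂) − z_α). Exact t-test values are given where they differ.

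**1. Reproducing the stated figure at 1:1**

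- One-sided 5%: 2 × (1.645 + 0.842)² / 0.0625 ≈ 198 per arm (exact t: 199). This matches 200.
- Two-sided 5%: 2 × (1.960 + 0.842)² / 0.0625 ≈ 252 per arm (exact t: 253, total 506). This does not match.
- Power at 200 vs 200: √(1/200 + 1/200) = 0.10 and 0.25/0.10 = 2.5. One-sided Φ(2.5 − 1.645) = 80.4% (exact t: 80.3%); two-sided Φ(2.5 − 1.960) = 70.5% (exact t: 70.3%).
- Dropout: 400 / 0.5 = 800. This step is correct.

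Two other unstated settings also give about 200 per arm: a two-sided 10% test (198), and a two-sided 5% baseline-adjusted analysis with correlation 0.45, since 252 × (1 − 0.45²) ≈ 201.

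**2. Applying the planned 2:1 split to 800**

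800 enrolled is about 533 vs 267. After 50% dropout that is about 267 vs 133. The standard error is √(1/267 + 1/133) ≈ 0.106, and 0.25/0.106 ≈ 2.356.

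| Reading | Power at 267 vs 133 |
|---|---|
| One-sided 5%, unadjusted | 76% |
| Two-sided 5%, unadjusted | 65% |
| Two-sided 5%, baseline correlation 0.45 | 75% |

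The loss does not depend on which reading is right. The variance of the difference is 4/N at 1:1 and 1.5/N + 3/N = 4.5/N at 2:1, a ratio of 1.125. Any setting that makes 400 correct at 1:1 therefore needs about 400 × 1.125 = 450 at 2:1, or 900 enrolled.

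**3. Requirement at 2:1 for 80% power**

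- One-sided 5%: 149 controls, 447 completers, 894 enrolled.
- Two-sided 5%, unadjusted: 189.0 controls by the exact t-test, rounded up to 190, so 190 + 380 = 570 completers and 570 / 0.5 = 1140 enrolled.

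**4. The planned 1200**

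After 50% dropout, 400 vs 200. √(1/400 + 1/200) ≈ 0.0866 and 0.25/0.0866 ≈ 2.887. Two-sided, unadjusted: Φ(2.887 − 1.960) ≈ 82%. One-sided: 89%.

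On the two-sided unadjusted basis, 1140 − 800 = 340 of the additional 400 are needed to reach 80%, which leaves 60. On the one-sided basis, 894 − 800 = 94 are needed.

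**5. Sensitivity to dropout**

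Modification of I Move reports that 607/987 (61.5%) of participants did not complete the 12-month questionnaire in the earlier study. At that rate 1200 leaves 462 completers, about 308 vs 154, and two-sided unadjusted power is about 72%.

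**The case against.** The strongest reply is that neither 400 nor 800 is the target. Enrolment is at least 1200, and at 2:1 with 50% dropout the smaller arm has the 200 used in the calculation. One can even read the steps as 400 + 400 enrolled at 1:1, with a further 400 added to the intervention arm, which gives 800 vs 400. That reading would explain how the numbers arose, and it confirms that 1200 is adequate for one outcome on the stated inputs. It does not make 800 sufficient under the allocation used. The article does not describe the steps that way, and it gives no power for the design it will run.

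A second reply is that alpha, sidedness and model are details that a condensed article may leave to a fuller document, and that the analysis may use the baseline measurement. An effect size assigned to each arm separately does suggest change from baseline. This has force. The absence of alpha is not itself the point here, and 70% power at 200 per arm cannot be stated as fact. The allocation mismatch remains, because it costs the same 12.5% in sample size whatever those settings are.

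A third reply is that the article never calls the extra 400 surplus power. That is fair, and the remaining margin of 60 holds only for a two-sided unadjusted 5% test.

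**Conclusion.** The 400/800 statement is wrong for the trial as randomised. At 2:1, 800 enrolled with 50% dropout gives 65% to 76% power across the three readings tried, against a stated 80%. The 2:1 shortfall needs no particular choice of alpha or sidedness, only that 400 was right at 1:1 and that dropout is equal between arms.

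The further gap between 200 and 253 per arm is conditional on an unadjusted two-sided 5% test. A reader might infer that a one-sided test was certainly used, but a two-sided 10% test or a baseline correlation of about 0.45 would give nearly the same number, and the article does not settle which.

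A reader might also infer that the trial is underpowered. The document does not support that: the planned 1200 gives about 82% for one outcome on the two-sided unadjusted basis at the assumed dropout and effect size. On that same basis, most of the step from 800 to 1200 is needed for nominal power and is not spare for incomplete module uptake.

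**What to change.** Rewrite the sample-size paragraph:

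- Redo the calculation at 2:1 and state alpha, sidedness and any baseline correlation assumed, with its source.
- If the test is two-sided 5% and unadjusted, give about 570 completers (380 vs 190) and 1140 enrolled at 50% dropout. If another setting was used, give the corresponding 2:1 figures.
- Drop the statement that 800 suffices.
- State the power of the planned design: about 82% for one outcome with 400 vs 200 completers on the two-sided unadjusted basis. Add that most of the increase from 800 to 1200 is then needed to reach 80%.

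The cost is one reworded paragraph. Enrolment and allocation do not change, but the reported reserve for module uptake becomes smaller.
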